## Abstract

**Background:**

Lymphoma survivors commonly report ongoing complaints including fatigue, pain, depression and decreased quality of life (QoL) following treatment. Although evidence suggests that both relaxation and exercise can significantly improve such symptoms, there is no consensus on which intervention is more effective. This paper presents the REIL (Relaxation and Exercise In Lymphoma) Study protocol. The REIL study aims to compare the effect of two home-based interventions – relaxation and exercise – on QoL in lymphoma survivors.

**Methods:**

Eligible participants (*n* = 36) will be randomised to a relaxation or exercise programme to perform at least three times per week. The primary outcome measure is QoL, assessed by the European Organisation for Research and Treatment of Cancer QoL Questionnaire Core 30 (EORTC QLQ-C30). Secondary outcome measures include body composition, cardiovascular status, pulmonary function, grip strength, functional exercise capacity (six minute walk test), well-being assessed by the FACT-Lym questionnaire, and psychological status assessed by the Hospital Anxiety and Depression Scale. Total duration of the study will be twelve weeks and outcome measures will be assessed at baseline, six weeks and at the end of the study.

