### Sample size

Sample size was calculated to determine clinically relevant effects on the primary outcome measure, the European Organisation for Research and Treatment of Cancer – QoL core questionnaire (EORTC QLQ-C30, version 3.0). A minimally important difference of 5 to 10 points is generally accepted as clinically meaningful [22], and calculations were based on comparison of means between two groups. Assuming a two-sided significance level level (α) of 0.05, power of 80% (ß = 0.20) and standard deviation from EORTC website reference values [23], it was determined that a sample of minimum 46 participants will be required to detect a significant change in the EORTC summary score, 23 in each intervention group.

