### Data analysis

Data will be entered into the Microsoft Excel (2013) database by SH and analysed by all authors using the IBM SPSS version 22 (SPSS, Inc., Chicago, IL) statistical software package. The intent-to-treat principle will be applied and the significance level will be set at 0.05. Descriptive statistics will be used to present baseline demographic characteristics. To compare difference in the primary outcome measure, QoL score between the two groups post-intervention, ANCOVA (analysis of covariance) will be used, with pre-test values as covariate to adjust for any baseline differences. Data will be analysed to check fit for ANCOVA assumptions. Post-hoc paired-samples t-tests for pre-post intervention will be tested within groups with Bonferroni corrections. Missing data will be treated as recommended by scoring guidelines of questionnaires [24, 30]. These analyses will be repeated for secondary outcome measures, providing data fit normal distribution and other assumptions for ANCOVA. The influence of potential confounding factors such as age, gender, number of co-morbidities and ECOG status will be explored using correlation analyses. Adherence and drop-out rates will also be analysed. Qualitative data from the end of study questionnaire will be analysed for codes and themes using qualitative content analysis [39].

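### The abstract randomises 36 participants, but the sample size section requires at least 46; if 36 is the true number, power on the article's own basis is about 69-70%, not 80%

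*Protocol article*

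**What the plan says.** The abstract, under Methods, gives the size of the trial as a number to be randomised: "Eligible participants (*n* = 36) will be randomised to a relaxation or exercise programme".

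The Sample size section gives a different figure: "a sample of minimum 46 participants will be required to detect a significant change in the EORTC summary score, 23 in each intervention group". It states the error rates ("Assuming a two-sided significance level level (α) of 0.05", with 80% power) and says that the calculation compares means between two groups. For the effect it says "A minimally important difference of 5 to 10 points is generally accepted as clinically meaningful", without fixing one value in that range. The SD is cited to an external reference and not given as a number.

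The Data analysis section makes ANCOVA, with the baseline value as covariate, the primary comparison. The Discussion defends the small sample by pointing to the power calculation. It does not mention 36.

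**The concern.** Both figures are current, forward-looking statements about the same trial. The smaller is 10 participants (10/46 = 22%) below a number that the article itself calls a minimum. A reader cannot tell whether the trial is meant to reach its own required size.

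The number randomised and the power for the primary outcome decide how a null result is read. If 36 are randomised while the text claims 80% power, a non-significant difference in quality of life would be taken as stronger evidence of no difference than the design supports. The article says that the study aims to determine the more effective of the two interventions, so that reading matters.

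**Working it through.** **Inputs.** 46 in total, 23 per group, two-sided α = 0.05, power 80%, comparison of two means (Sample size section). 36 randomised (abstract), taken as 18 per group because the Sample size section implies equal groups.

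**Can 46 be reproduced?** Not forwards, because neither the SD nor the single difference used is given. It can only be solved backwards. The comparison of 36 with 46 does not need the missing values: fixing 80% power at 23 per group fixes the standardised difference d, and power at d then depends only on n.

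**Step 1: the difference for which 23 per group gives 80%.**
- Normal approximation: d = (z₀.₉₇₅ + z₀.₈₀) × √(2/n) = (1.960 + 0.842) × √(2/23) = 0.826.
- t-test (noncentral t, 2n − 2 degrees of freedom, noncentrality d√(n/2)): d = 0.845.

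**Step 2: power at 18 per group for the same difference.**
- Normal approximation: d√(n/2) − 1.960 = 0.826 × 3 − 1.960 = 0.518, and Φ(0.518) = 69.8%.
- t-test with d = 0.845: 69.2%.

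**Step 3: the difference for which 18 per group gives 80%.**
- Normal approximation: (1.960 + 0.842) × √(2/18) = 0.934 SD.
- t-test: 0.961 SD.

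**Step 4: what ANCOVA could recover at 18 per group.** Adjusting for a baseline value with correlation r to the 12-week value multiplies the residual SD by √(1 − r²), so the effective difference is d/√(1 − r²). This ignores the one degree of freedom spent on the covariate.

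| r | Power at 18 per group (t-test, d = 0.845) |
|---|---|
| 0 | 69.2% |
| 0.30 | 73.3% |
| 0.40 | 76.6% |
| 0.45 | 78.7% |
| 0.50 | 81.1% |
| 0.60 | 86.8% |

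The break-even point solves 0.845/√(1 − r²) = 0.961. That gives 1 − r² = (0.845/0.961)² = 0.773, so r is about 0.48.

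**Step 5: could 36 and 46 be two views of one calculation?**
- A one-sided 0.05 test at the same difference needs about 18 to 19 per group, 36 to 38 in total. The section states a two-sided test.
- 36/(1 − 0.20) = 45, close to 46, so 46 might look like 36 enlarged for drop-out. The section presents 46 as the result of the power calculation and mentions no enlargement. The abstract also attaches 36 to randomisation, whereas an enlarged figure would itself be the number randomised.

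Neither route is supported by the text.

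**The case against.** The strongest reply is that 36 is a slip. It appears once in the text shown, in the abstract, while the operative section gives 46 with its breakdown by group and the Discussion defends the calculated size. If so, 80% is met on the article's own basis and the defect is one wrong number. This stands as far as it goes: the document does not settle which figure is the target. The contradiction still has to be corrected, because the abstract says how many will be randomised.

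A second reply is that the primary test is ANCOVA, so the unadjusted 69-70% is a low estimate of the power at 36. That is fair. The figure measures the shortfall against the article's own calculation. Under the planned analysis neither adequacy nor shortfall at 36 is established, because no correlation is stated.

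A reader might also infer that 46 is too few because it carries no drop-out margin, especially as "Adherence and drop-out rates will also be analysed". The document does not support this. Reporting drop-out is not a statement that a given level is expected, no rate is given, 46 is labelled neither randomised nor analysed, and a condensed article may leave an allowance to the full protocol. Nor can the detectable difference be converted into questionnaire points, since the section gives a range of 5 to 10 and does not say which value was used.

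**Conclusion.** The point holds as a contradiction between two sections, with a conditional consequence for power. The abstract and the Sample size section give sizes that differ by 10 participants, and nothing reconciles them.

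If 36 is the true number, power is about 69-70% where the article claims 80%, and 80% needs 0.93 to 0.96 SD in place of 0.83 to 0.845 SD (normal approximation to t-test). This rests on equal groups, two-sided 0.05, the unadjusted comparison that the article describes, and all 36 being analysed. It does not depend on the missing SD. With ANCOVA, 80% at 36 would need a correlation of about 0.48 or more.

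Two stronger readings are not supported. One is that the trial is underpowered as a matter of fact, which is true on the article's basis only if 36 is the target. The other is that 46 was miscalculated, which cannot be tested from the inputs given.

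**What to change.** State one number throughout.

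- **If 46 is the target:** replace 36 in the abstract, and in the flow diagram if it carries 36 (the figure is not available here). The Sample size section can stand on this point.
- **If 36 is what will be randomised:** restate the Sample size section as about 69% power for the planned difference, or 80% power for a difference of 0.96 SD, on the unadjusted basis. Alternatively, give the ANCOVA power with the assumed baseline to 12-week correlation and its source.

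The cost is a change of wording in one or two places. If 36 is the true number, the stated power becomes less favourable. If recruitment has been planned for 36 and 46 is adopted, ten more participants are needed.

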**Discussion:**

It is anticipated that results from this preliminary study will begin to highlight effective pathways to improve QoL following chemotherapy for this population. This will better inform healthcare professionals to optimise QoL of lymphoma patients, and enable a smooth transition from being a cancer patient to survivor.

**Trial registration:**

The REIL study has been registered on a publicly accessible database, ClinicalTrials.gov, Registration Number: NCT02272751, October 2014.

## Background

Significant improvements have been made in the survival rates in cancer patients due to earlier detection and advances in treatment. Although initial research in the field of cancer survivorship focused on tumours such as breast and prostate, dramatic advances in haematological malignancies have also led to increased survival [1], but at a cost of increasing complications. Like survivors of other cancers, lymphoma survivors are at an increased risk of morbidity and adverse effects due to disease and treatment exposures. Commonly reported long-term and late effects of treatment in lymphoma survivors include both physical and psychosocial symptoms such as fatigue, pain, muscle weakness, neuropathies, depression, anxiety and decreased self-esteem; as well as decreased function and quality of life (QoL) [1–3]. Hence there has been a call for further research to address the ongoing needs of lymphoma survivors [1].

When medical treatment is completed successfully and the patient is in clinical remission, the close support from medical staff is usually reduced and the patient is expected to return to ‘normal life’. This transition however does not always occur smoothly and studies have highlighted that post-treatment survivors at this transition phase often feel unprepared and uninformed [1, 3]. Survivors at this phase are sometimes in need of further support and advice on how to progress activity, manage ongoing symptoms and return to pre-morbid status and often do not receive this [2, 3]. There are currently no recommended care pathways for lymphoma patients in remission following treatment, despite the fact that this transition period shortly after treatment has been highlighted to be particularly difficult [4].

This lack of care pathways has been highlighted by the government in the United Kingdom (UK). The National Cancer Survivorship Initiative (NCSI) was launched in 2008 and calls for research into the development of pathways for cancer survivors [5], recommending holistic assessment and personalised care-planning, emphasis on the use of patient-reported outcome measures and a shift towards self-management [6].

Self-management in cancer survivorship has been defined as ‘awareness and active participation by the person in their recovery, recuperation and rehabilitation, to minimise the consequences of treatment, and promote survival, health and well-being” [7]. Increasing numbers of survivors together with limited healthcare resources has led to a focus on self-management as an important approach for cancer survivors. Furthermore, self-management can empower cancer patients, increase their confidence to manage problems associated with disease and treatment, and enhance QoL [8].

Literature indicates that interventions such as relaxation and exercise both have a positive impact on QoL of cancer survivors [9–12]. It has been demonstrated that exercise interventions have a positive impact on physical and psychological factors related to QoL such as peak oxygen consumption, physical functioning, fatigue, self-esteem and social functioning; as well as overall QoL of cancer patients and survivors [9, 10]. Studies on relaxation interventions including mindfulness-based stress reduction and progressive muscular relaxation have also demonstrated significant positive impact on physical and psychological symptoms such as fatigue, pain, anxiety and depression, as well as on QoL in cancer survivors [10–12]. Hence both relaxation and exercise interventions are recommended by organisations providing expert advice and support to cancer patients and survivors such as Lymphoma Action [13] and Macmillan Cancer Support [14].

However in the majority of trials studying the effects of relaxation or exercise on cancer survivors, the benefits have only been relative to a control group; and to rule out potential placebo effects future studies need to specify more rigorous comparison conditions, for instance a control intervention with similar elements that may influence outcome such as attention from study personnel or time spent on the procedure [15, 16]. Hence there has been a call for further studies to move beyond wait-list control groups and to compare with active control or other empirically supported interventions [15, 16], for instance relaxation to exercise. As a result, there have been studies and study protocols looking at comparison of two interventions in cancer survivors, but the majority of these have focused on breast cancer [17, 18] and authors have called for future research to focus on other survivor groups, including haematologic cancer sites [1, 19].

The REIL study aims to address some of these issues highlighted by studying a sample of lymphoma survivors post-chemotherapy, supporting patients during the transition phase, comparison of two interventions, use of patient-reported outcome measures and emphasis on self-management. Results from this preliminary study would provide an indication of efficacy of interventions, and with the findings from the REIL study we aim to build towards the development of evidence-based practice guidelines for lymphoma survivors.

This paper presents the REIL study protocol using SPIRIT 2013 guidelines [20].

### Aims

The primary aim of the REIL Study is to compare the effect of two interventions – relaxation and exercise – on QoL in a sample of lymphoma patients in remission post-chemotherapy. The null hypothesis is that there is no difference in QoL between the relaxation and exercise groups post-intervention.

Secondary aims are to investigate the effects of the two interventions on body composition, cardiovascular status, pulmonary function, muscle strength, functional exercise capacity, well-being and psychological status; and explore perceptions about participation in the post-treatment intervention programme.

## Methods

### Study design

The REIL study is a prospective, randomised, clinical intervention trial. Participants will be randomised to exercise or relaxation intervention. Participants will be assessed at baseline prior to commencing the intervention programme, at six weeks, and at the end of the twelve week intervention.

### Ethical approval

The REIL study has received ethical approval from Camden and Islington National Research Ethics Service (13/LO/1327), who are the responsible for approval of final protocol as well as any modifications or amendments. Local site approval from St. George’s Hospital Joint Research and Enterprise Office (JREO) has also been obtained (13.0108). The JREO is an independent office providing external review and monitoring of any research undertaken at St. George’s NHS Trust in order to maintain clinical research governance guidelines and standards.

The study has been registered on a publicly accessible database, ClinicalTrials.gov, NCT02272751.

### Recruitment

Participants will be recruited from a single specialist clinical setting – the Haematology-Oncology Out-Patient (HOOP) Clinic at St George’s Hospital, London. Assessment for eligibility, recruitment, medical screening and obtaining of informed consent will be carried out by the patients’ medical consultant (RP). In order to encourage participant enrolment, potential participants will be introduced to the principal investigator (SH) who will explain about the study, answer questions and provide with the written participant information sheet to take away and read before making a decision.

### Eligibility criteria

Inclusion criteria include patients with histologically confirmed lymphoma in remission post–chemotherapy, chemotherapy treatment completed within the last six weeks, age 18 years or older, able to give informed consent, good performance status (assessed by the Eastern Cooperative Oncology Group {ECOG} status 0–2) [21] and medically able to carry out an exercise training programme. Patients with active disease, unstable angina or unexplained electrocardiogram, poor performance status (ECOG status 3 or more), pregnancy, difficulty breathing at rest, persistent cough, fever or illness, or any cognitive impairment limiting ability to give informed consent or complete QoL questionnaires will be excluded. Written informed consent will be obtained from all individual participants included in the study.

### Sample size

Sample size was calculated to determine clinically relevant effects on the primary outcome measure, the European Organisation for Research and Treatment of Cancer – QoL core questionnaire (EORTC QLQ-C30, version 3.0). A minimally important difference of 5 to 10 points is generally accepted as clinically meaningful [22], and calculations were based on comparison of means between two groups. Assuming a two-sided significance level level (α) of 0.05, power of 80% (ß = 0.20) and standard deviation from EORTC website reference values [23], it was determined that a sample of minimum 46 participants will be required to detect a significant change in the EORTC summary score, 23 in each intervention group.

### Randomisation

A random allocation list will be prepared by the department statistician, generated using GraphPad randomisation software (GraphPad Prism version 6.04 for Windows, GraphPad software, CA). On entry into the study each participant will be assigned an anonymous ID number and each number will be allocated an intervention (exercise or relaxation) on the list. As all assessment sessions will be carried out by the single principal investigator (SH), it will not be possible to blind the investigator to intervention. Also due to the nature of the intervention participants cannot be blinded to group allocation.

Flow of participants in the study is shown in Fig. 1.

**Fig. 1 Fig1:**
[figure not shown]
Flow of participants in the REIL Study. CONSORT flow diagram demonstrating participant flow through each phase of the randomised controlled trial (enrolment, intervention allocation, follow-up and data analysis)

### Interventions

Interventions for this study are reported using the template for intervention description and replication (TIDieR) checklist and guide [24].

For both groups, advice, instruction, demonstration and practice will be carried out at baseline. This will be delivered by the principal investigator SH, an experienced physiotherapist with a special interest and experience in oncology. Participants will be able to contact SH by telephone in between sessions if additional support is required. All participants will be advised on potential adverse events and what to report including pain, fatigue, muscle soreness, lymphoedema, nausea, dyspnoea, dizziness, tachycardia and cramp. A logbook will be provided to all participants to encourage adherence and document self-reported participation levels, intervention type carried out, frequency, intensity, duration and any adverse events.

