#### Relaxation intervention

The relaxation intervention consists of a bed- or chair-based program, developed based on the literature on mindfulness-based interventions in cancer survivors [10–12]. An audio CD was produced to guide participants through relaxation techniques incorporating mindfulness meditation, breathing exercises, guided visualisation and progressive muscle relaxation. Here also participants will be advised to carry out the programme for 50 min three times a week. Participants will also be provided with written information on relaxation and tips on how to incorporate into daily life. Participants in this group will not be advised to perform any exercise outside of their normal habits, nor asked to avoid activity.

Participants will be followed-up at six weeks, midway through the programme. At this stage all assessments will be repeated, any change noted and they will be advised on how to modify the programme (relaxation or exercise) as appropriate. Once participants have completed twelve weeks of their intervention, they will be provided with resources of the other intervention group, for their information or to carry out as desired, in accordance with the Declaration of Helsinki.

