While the additional psychosocial benefits of supervised group classes for cancer survivors have been recognised [44], the need for a shift towards self-management in cancer survivorship has been highlighted [6, 7]. Here participants are supported to self-manage in a variety of ways, but the onus will be on them to initiate contact with the healthcare professionals for additional support when needed [7, 8]. Both the relaxation and exercise programmes in this study are designed to be performed independently and participants will be supplied with resources to allow convenient home-based performance, including written instructions and advice. Participants will be able to contact the investigator whenever required. This study will provide results including adherence and drop-out rates that are more generalizable to ‘real-world’ lymphoma survivors than controlled clinic-based research. Home-exercise programmes also afford patients better scheduling flexibility, familiar surroundings, family support and reduced travel requirements [45].

It will not be possible to stratify participants by factors such as age, gender, etc. during randomization due to the small sample size. However, sample size was calculated using reference values (including standard deviation) and power calculations recommended by the EORTC reference manual [23]; similar trials on the effects of exercise in cancer patients have been carried out with comparable sample sizes, and these were able to detect significant results [9].

In addition to quantitative data from outcome measures, the end of study questionnaire will explore participants’ perceptions and feelings towards an intervention programme post-chemotherapy. Such information will highlight behaviours and patterns in this sample of lymphoma survivors including reasons for participation, adherence and non-adherence, and any preferences; it is anticipated that this data will ultimately help in the promotion of a healthy lifestyle in lymphoma and cancer survivors.

The authors will aim to publish results from this study to add to the evidence to inform healthcare professionals on effective interventions to improve QoL of lymphoma survivors.

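### The stated adverse-event record is a self-completed adherence logbook plus participant reporting, with no scheduled enquiry at visits or withdrawal, so it is likely to be least complete for participants who stop

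*Protocol article*

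**What the plan says.** The Interventions section describes the logbook: "A logbook will be provided to all participants to encourage adherence and document self-reported participation levels". Its listed contents end with "intervention type carried out, frequency, intensity, duration and any adverse events". The same section says "All participants will be advised on potential adverse events and what to report including pain, fatigue, muscle soreness", and goes on to lymphoedema, nausea, dyspnoea, dizziness, tachycardia and cramp, making nine symptoms. It names no recipient and no timing for these reports. Between visits, participants may telephone the investigator if they want more support. The Discussion sets this in a self-management rationale in which "the onus will be on them to initiate contact with the healthcare professionals for additional support when needed".

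Visits take place at baseline, 6 weeks and 12 weeks. Of week 6, the article says "At this stage all assessments will be repeated, any change noted". Table 1, which summarises the outcome measures and when each is taken, has no adverse-event row. The Data analysis section covers QoL, the secondary outcomes, possible confounders and the qualitative data. The nearest it comes to harms is "Adherence and drop-out rates will also be analysed".

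**The concern.** Participants start an unsupervised home programme soon after chemotherapy, and the trial wants to learn which of two programmes does more for QoL, as a step towards practice guidelines. A reader of that result will also want to know how well each programme was tolerated.

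The instrument named for recording events is a diary of sessions. A participant who gives up the programme has no sessions left to enter and little reason to keep the diary. Completeness is therefore likely to fall among those who stop, and some of them may stop because of an event. The two arms differ in physical demand: one does moderate-intensity walking and resistance work, the other a bed- or chair-based programme. Loss of records need not be equal between them. Events not recorded at the time are hard to recover afterwards.

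A lesser point concerns baseline. The Background lists as common after treatment "physical and psychosocial symptoms such as fatigue, pain, muscle weakness, neuropathies, depression, anxiety and decreased self-esteem", and pain and fatigue are also on the list of events to report. No baseline record in the terms of that list is stated, which makes new or worsened events harder to identify.

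**Working it through.** The plan gives no figure on this point, so the check sets the possible routes for capturing harm side by side and then asks what incomplete recording could do.

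**Routes by which harm could be recorded**

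- Logbook (Interventions): names adverse events, is self-completed and is tied to sessions. Return of logbooks by participants who stop is not described.
- Participant report (Interventions): both arms are told what to report. To whom and when is not stated.
- Telephone contact (Interventions, Discussion): started by the participant and described as support.
- Visits at 6 and 12 weeks (Relaxation intervention, Outcome measures): the listed assessments are repeated. Table 1 has no adverse-event item, and no set questions on events are described.
- End of study questionnaire: open-ended, on preferences, disadvantages and reasons for adherence. Its own section places it at the final assessment, whereas Table 1 says it is mailed home. If it is given only at the visit, it misses participants who have left.
- Drop-out rates (Data analysis): show how many left, not whether an event was the cause.

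The logbook and the instruction on what to report are the two routes that name adverse events, and both depend on the participant acting.

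**What incomplete recording could do (assumed figures)**

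Let p be the true proportion with an event in an arm, and s the share of those participants whose event goes unrecorded. The recorded rate over all randomised is p × (1 − s). With p assumed to be 30%:

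- s = 25%: 0.30 × 0.75 = 22.5%
- s = 50%: 0.30 × 0.50 = 15%
- s = 75%: 0.30 × 0.25 = 7.5%

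For the comparison between arms, the recorded ratio (exercise to relaxation) equals the true ratio × (1 − s in exercise) / (1 − s in relaxation):

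- loss of 50% in exercise only: multiplied by 0.5 / 1 = 0.5
- loss of 50% in both arms: multiplied by 0.5 / 0.5 = 1
- loss of 50% in relaxation only: multiplied by 1 / 0.5 = 2

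Loss lowers the recorded rate in any arm where it occurs. The ratio can move either way or stay the same. The article gives no value for p or s in either arm.

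**What complete data could show**

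The Sample size section gives 23 per arm. The Abstract gives 36 in total, which is 18 per arm if split equally, so both are shown.

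- With no events in an arm, the one-sided 95% upper bound on the rate is 1 − 0.05^(1/n): 12.2% for n = 23 and 15.3% for n = 18.
- Under assumed rates of 10% and 30%, a two-sided 5% test of two proportions (normal approximation) has power of about 39% with 23 per arm and 32% with 18.

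Even with full capture, a comparison of harms at this size can only be descriptive.

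**The case against.** The strongest reply is that this is an article, not the full protocol. How events are asked about at visits, followed up at withdrawal and tabulated is commonly left to documents not shown here. That stands for the analysis. A reader might infer that the arms will never be compared on harm, but the text supports no more than that no such comparison is stated.

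A reader might also infer that harm can surface only through the logbook or a call the participant makes. That goes too far. The investigator sees participants at 6 and 12 weeks and notes change, and the end of study questionnaire may bring out reasons for stopping. The Discussion's sentence on who starts contact concerns support and is not a rule for reporting events.

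A third tempting reading is that a logged symptom cannot be told from a pre-existing complaint. Medical history is taken at baseline. Resting heart rate, oxygen saturation, the questionnaires and post-walk dyspnoea are collected at all three visits. What is not stated is a baseline record in the same terms as the symptom list.

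Finally, an event comes before the stop that it causes, so it may already be in the logbook, and nothing says that logbooks are not collected from those who leave. Loss among those who stop is therefore a reasonable expectation, not a demonstrated fact.

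What remains is a point about something the article does state. It names its method for recording events, and that method is weak where completeness matters most.

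**Conclusion.** The point holds in a limited form. The stated capture of adverse events rests on a self-completed adherence logbook and participant reporting. No scheduled enquiry is stated at 6 or 12 weeks or at withdrawal, and adverse events are in neither Table 1 nor the Data analysis section. The record is likely to be least complete for participants who stop, and the shortfall may differ between arms.

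This rests on one assumption that the article cannot confirm: that diary-keeping tends to lapse when the programme does. The size and the net direction of any bias between arms are unknown, so it would be wrong to conclude that harms in the exercise arm will be undercounted relative to relaxation. The QoL analysis is not affected. For a trial that calls itself preliminary, this is an inexpensive improvement in measurement, but one that has to be made prospectively.

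**What to change.** Turn the nine symptoms in the Interventions section into a fixed checklist. Ask it in the same words in both arms at baseline, 6 weeks and 12 weeks, and in one telephone call when a participant withdraws, together with the reason for stopping. Identical wording matters because the investigator who carries out the assessments is unblinded and also delivers the instruction in both programmes. Keep the logbook as a supplement.

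Add an adverse-event row to Table 1. In the Data analysis section, state that the number of participants with any new or worsened event since baseline, and the reasons for stopping, will be summarised by arm beside the QoL result, without a formal test. If the full protocol already provides for this, a sentence in the article saying so is enough.

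The cost is one checklist page at visits that already take place, one call per withdrawal and one descriptive table. The downside is a few minutes per visit and more minor events recorded.
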